## Discussion

The main objective of this randomised controlled trial is to determine the effectiveness of two physiotherapy protocols in improving balance and decreasing pain in women with FM, at the end of the intervention and at 6-weeks follow-up. With the study conclusion, we expect to test the following null hypothesis: “There is no difference in balance or pain for participants undergoing physiotherapy interventions on land or in water”. The balance disorder observed in FM is a sympton that has been discovered only recently. This is why there are very few publications regarding. Specifically, in the MEDLINE database, we were able to identify only 11 randomized controlled trials that included physical interventions and balance improvement was included in their objectives. Of these 11 clinical trials, only three included physiotherapy as a treatment method [43–45]. Given this, we expect the study conclusion to contribute to the fund of scientific knowledge, providing evidence that physiotherapy is a safe and effective tool in the management of FM symptoms, specifically balance disorders and pain.

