## Background

Fibromyalgia (FM) is a chronic disorder characterized by widespread pain in combination with tenderness in at least 11 of 18 established tender points [1]. In 2010, following the release of the new diagnostic criteria of the American College of Rheumatology (ACR) [2], a new definition for FM was adopted. In addition to pain, it includes other important symptoms such as fatigue, restless sleep, cognitive problems and a variety of somatic symptoms.

The mean prevalence rate of FM in Europe is 2.5% [3], and the prevalence in Spain in those greater than 20 years of age is 2.4% [4]. Worldwide, the incidence of FM is increasing at an exponential rate, demonstrating that FM is a common clinical condition that will require increasing specialised attention. FM causes disability, which is associated with high indirect costs derived from absenteeism and the use of health care resources. This is not only a major health problem, but also a significant socioeconomic problem [4]. There are many available treatments to manage FM, however, only a few are supported by scientific evidence. The latest report of the European League Against Rheumatism (EULAR) [5] agrees with current clinical practice guidelines (CPG) which state that aerobic exercise is the only treatment option for the management of FM based on strong scientific evidence. CPG from Germany and Israel consider aquatic therapy as the best aerobic exercise program for this type of patient [6] however, for the EULAR, the effectiveness of exercise does not depend on the environment where it is performed (in or out of water).

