### Inclusion criteria

Female.Age range between 35 and 64 years [17].FM diagnosis according to the ACR criteria: 1990 [1] and 2010 [2].Mark ≥ 4 on “Visual Analogue Scale” (VAS) for pain.Mark ≥ 5 on EVA for balance, included in the “Revised Fibromyalgia Impact Questionnaire” (FIQR).

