### Randomisation

Once the patients have read and signed the informed consent, those who have met the inclusion criteria, will be randomly assigned to one of the two intervention groups:Active Control Group: Land-based exercise program (CG *n* = 20).Experimental Group: Water exercise program (EG *n* = 20).

The randomisation will be carried out in a 1:1 manner via a computer-based scheme. The allocation will be concealed using sealed and opaque envelopes, numbered consecutively [18]. An independent researcher who will not participate in other study procedures will perform the randomisation process. The flow diagram of the study is summarised in Fig. 1.

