### Interventions

The interventions designed in this protocol consist of two similar physiotherapy protocols for people with FM. Both will include 60-min sessions that will be carried out 3 times a week for 3 months by a physiotherapist, in groups of 8–9 people maximum.

Both interventions will be based on: 15 min of warm-up, 25 min of proprioceptive exercises, 8 min of stretching and 12 min of relaxation.

For adequate training of balance and postural control, patients will be required to contract their local musculature (“core stability”) before starting any specific exercise. The transversus abdominis, pelvic floor muscles, internal oblique and multifidus form the local musculature. The most important aspect of achieving core stability will be co-activation of the first two muscles, for which patients will have to place their pelvis in a neutral position. Before starting the interventions, patients will receive anatomy and palpation classes to aid in identification of the involved musculature and how its contraction is perceived.

The protocols have been created by the main researcher based on available scientific evidence. The protocols were designed with the intention of being as similar as possible in order to attribute any statistically significant difference in outcomes between the two groups to the environment where the interventions were performed. Sessions will be pre-programmed with a progression in difficulty over the intervention period: Shorter pauses, higher exercise intensity, eyes closed, etc.

Patients will not be allowed to begin any other activity during the study period. They will have to report any problems, whether event-related or not, as well as any medication changes.

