### Statistical analysis

Analysis will be descriptive of all outcomes included in the study, expressing quantitative outcomes with their mean ± standard deviation and qualitative outcomes with their absolute value, percentage and 95% confidence intervals.

The association between qualitative outcomes will be studied using the Chi-square test. After checking normality with the Kolmogorov-Smirnov test, the Student *T* test or the Mann–Whitney *U* test will be used to perform mean comparison. The mean comparison between two or more categories will be studied with the ANOVA test or Kruskal-Wallis test, as appropriate.

The correlation between quantitative outcomes will be analysed with the Pearson or Spearman correlation coefficients, as appropriate.

The mean comparisons for related outcomes in two different moments will be studied with the Wilcoxon test. Friedman test will be used when comparing more than two moments. In addition, the clinical relevance of the intervention will be studied by calculating the relative risk, relative risk reduction, absolute risk reduction and the number needed to treat. All of these measures will be presented with their 95% confidence interval.

A multivariate analysis by multiple linear regression or logistic regression to adjust for the effectiveness of the intervention according to possible confounding factors and to determine what other outcomes might be associated with each result will be carried out. Only the outcomes that show a statistical significance p <0.20 in the bivariate analysis, will be included in the multivariate regression analysis. In addition, a stepwise backward modelling strategy will be carried out.

All analysis will be done by intention to treat [42], where the total value of randomisation is preserved and control of any counfounders’ effect is insured.

The significance level set for all the analysis will be *p* ≤0.05. The SPSS statistical software, version 21.0 (SPSS, Chicago, IL) will be used for all analysis.

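### The objective and expected conclusion claim that physiotherapy works, but the only randomised contrast is water versus land

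*Protocol article*

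**What the plan says.** The Abstract, the end of the Background and the Discussion all state the main objective in absolute terms. The Discussion words it as "determine the effectiveness of two physiotherapy protocols in improving balance and decreasing pain in women with FM". It names two time points, one when treatment ends and one six weeks later. The same section hopes that the study will contribute by "providing evidence that physiotherapy is a safe and effective tool in the management of FM symptoms".

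The design is comparative. Under Randomisation, the comparator is "Active Control Group: Land-based exercise program", with 20 patients against 20 in water. Under Interventions, "The interventions designed in this protocol consist of two similar physiotherapy protocols for people with FM"; any significant difference between the groups is to be attributed to the environment. The null hypothesis in the Discussion is "There is no difference in balance or pain for participants undergoing physiotherapy interventions on land or in water". No untreated, usual-care or sham arm is described.

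Statistical analysis plans Wilcoxon tests for two time points and Friedman tests for more than two. Inclusion criteria require a pain VAS of at least 4, and pain intensity on that scale is also a primary outcome.

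**The concern.** The objective and the expected conclusion concern physiotherapy as such. The randomised comparison concerns the medium in which it is delivered. No analysis plan can close that gap, because the missing element is a comparator and not a method.

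The only data bearing on the absolute question are before-after changes, and tests of those changes are planned. If both arms improve significantly and do not differ, the objective as worded invites the conclusion that both programmes are effective. The trial could not support that. What is at stake is the headline conclusion, not the conduct of the study.

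**Working it through.** **1. Which data answer which question**

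| Question | Evidence in this design | Randomised? |
|---|---|---|
| Does water differ from land in pain or balance? | Between-arm comparison | Yes |
| Does either programme, or physiotherapy in general, improve pain or balance? | Change within each arm (Wilcoxon, Friedman) | No |
| Is physiotherapy safe? | Problems that patients report (Interventions); no safety measure among the listed outcomes | Between arms only |

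The objective and the expected conclusion fall in rows 2 and 3. The null hypothesis, the attribution to environment and the sample size fall in row 1.

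**2. The plan's own figure**

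Inputs from Sample size calculation: difference 2.5 VAS points, SD 2.5, two-sided 0.05, power 80%, dropout 20%.

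n per arm = 2 × (1.960 + 0.842)² × (2.5/2.5)² = 15.7, so 16 evaluable; 16/0.8 = 20 enrolled.

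The TUG inputs (2 s, SD 2 s) have the same ratio and give the same numbers. The stated 20 per arm reproduces by the normal formula. An exact t calculation gives 17 evaluable per arm, which is close. The figure is a between-arm calculation, so it also belongs to row 1.

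**3. Regression to the mean in pain**

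Expected fall with no treatment effect = (1 − r) × SD × φ(z)/(1 − Φ(z)), where z = (4 − mean)/SD.

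The cut-off of 4 is from Inclusion criteria. The SD of 2.5 is from Sample size calculation, taken here as the unselected SD. The documents do not give the population mean or the retest correlation r, so both are assumed. The formula also assumes normality and that the screening score serves as baseline.

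| Assumed mean | z | SD × φ/(1 − Φ) | Fall, r = 0.4 | Fall, r = 0.8 |
|---|---|---|---|---|
| 5 | −0.4 | 1.40 | 0.84 | 0.28 |
| 6 | −0.8 | 0.92 | 0.55 | 0.18 |
| 7 | −1.2 | 0.55 | 0.33 | 0.11 |

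The range is about 0.1 to 0.8 points, or 4% to 34% of the 2.5-point planning difference. Natural course and placebo response come on top and cannot be sized from the documents.

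**4. What a non-significant water-land result would leave open**

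95% half-width = t(0.975, 30) × SD × √(2/16), with t = 2.042.

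- Pain: 2.042 × 2.5 × 0.354 = 1.81 points.
- TUG: 2.042 × 2 × 0.354 = 1.44 s.

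Each is 72% of its planning difference (1.81/2.5 and 1.44/2). With all 20 per arm the half-widths are 1.60 points and 1.28 s. No equivalence margin is stated.

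**The case against.** The best defence is that the sentence is a hope voiced in a Discussion, while the hypothesis, the sample size and the attribution to environment are already comparative. The analysis section never equates within-arm tests with effectiveness; it uses that word for the adjusted regression. This is true, and it is why the remedy is only wording. It does not dispose of the point, because the main objective carries the same absolute wording in three places.

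A second defence is that the Background says both kinds of programme have shown benefit, so a win for water over land would be indirect evidence for aquatic therapy. That is fair as far as it goes. However, it relies on outside studies whose quality the Background itself questions, and it would not help for land therapy or if the arms do not differ.

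Several stronger readings are tempting but not supported:

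- **That the plan would treat a null result as equivalence.** It nowhere says so. Step 4 is a caution about interpretation.
- **That mean differences will lack confidence intervals.** The phrase "expressing quantitative outcomes with their mean ± standard deviation" describes descriptive presentation. A condensed article may leave intervals for differences to the full documents.
- **That the Background predicts no difference.** It reports one body's view that "the effectiveness of exercise does not depend on the environment where it is performed", but the same sentence reports German and Israeli guidelines favouring aquatic therapy. Conflicting guidance is a reason to run the trial.
- **That regression to the mean also distorts the primary balance outcomes by a known amount.** The criterion "Mark ≥ 5 on EVA for balance" applies to one self-rated FIQR item. The primary balance outcomes are Romberg, TUG and gait measures, none of which is used for selection, and no SD is given for that item.
- **That patients are selected for high pain.** By the protocol's own bands, 4 to 7 is moderate.
- **That safety is ignored.** Patients must report problems and medication changes, and a fuller protocol may define more.

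The regression figure is also conditional. If baseline is measured separately from screening, much of the fall occurs before baseline.

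**Conclusion.** The point holds as a mismatch between the stated objective and expected conclusion on one side and the design on the other. The trial can support a relative statement about water versus land. It cannot show that physiotherapy, or either programme, is effective, because only uncontrolled change speaks to that.

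The absence of a non-physiotherapy comparator is the main reason and needs no assumption. Regression to the mean is a secondary contributor for pain only. Its direction is firm; its size, about 0.1 to 0.8 VAS points, rests on the assumed mean, correlation and normality, and on the screening score being the baseline.

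The half-widths of about 1.8 points and 1.4 s rest on the planning SDs and 16 evaluable patients per arm. If selection at VAS 4 or more narrows the spread of scores, the pain interval would be somewhat shorter.

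A reader might infer that the sample size is wrong or that equivalence is being claimed. The document supports neither.

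**What to change.** - Restate the objective in the Abstract, Background and Discussion as the difference between the water and land programmes in pain and balance, at the end of treatment and at 6-week follow-up.
- State that within-arm changes are descriptive and will not be presented as evidence of effectiveness.
- Replace the Discussion sentence on safety and effectiveness with a comparative one, and tabulate reported problems by arm.
- Add a sentence that a non-significant difference will not be read as equivalence.

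The cost is wording only: no new data, patients or design change. The downside is a more modest claim.

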## Abbreviations

ABC: Activities-specific balance confidence
ACOFIFA: Fibromyalgia, chronic fatigue syndrome and multiple chemical sensitiviy association
ACR: American College of rheumatology
ADL’s: Activities of daily living
AP: Anterior-posterior
CG: Control group
CPG: Clinical practice guidelines
EG: Experimental group
FIQ: Fibromyalgia impact questionnaire
FIQR: Revised fibromyalgia impact questionnaire
FM: Fibromyalgia
HR: Heart rate
MFI: Multidimensional fatigue inventory
ML: Medio-lateral
PSQI: Pittsburgh sleep qualitiy index
TUG: Timed up & go test
VAS: Visual analogue scale
